### 3.9. Laboratory measurements

Blood pH, natremia, kaliemia, lactatemia, and serum osmolality are measured at baseline (before skin incision), and at 30 minutes, 60 minutes, 180 minutes, 24 hours, and 48 hours after the end of osmotherapy (either mannitol or hypertonic sodium lactate) to describe the effect of hypertonic sodium lactate infusion on acid–base balance, electrolytes, and osmolality.

Serum levels of S100B and NSE proteins are measured at baseline (the day before surgery) and at 24 hours and 48 hours after the end of osmotherapy to assess postoperative brain ischemic changes.

### 3.10. Safety

All serious adverse events are collected and reviewed by the principal investigator and reported to the trial sponsor (CHU Besancon, Besancon, France), to the Pharmacovigilance Department of our institution and to the independent Data Safety and Monitoring Board (DSMB). Study insurance has been contracted for all participants by the trial sponsor (CHU Besancon, Besancon, France).

Since off-labeled use of hypertonic sodium lactate is prescribed in patients included in the interventional group. All serious adverse events will be reviewed and analyzed by the independent DSMB after the inclusion of the first 25 patients to decide whether the study should be stopped prematurely for safety reasons.

### 3.11. Sample size calculation

No previous study has assessed the clinical effectiveness of hypertonic sodium lactate infusion for intraoperative brain relaxation in patients undergoing scheduled craniotomy for supratentorial brain tumor resection. Thus, no assumption can be made on the expected difference in primary outcome between groups. The sample size calculation was based on the expected measurement accuracy of the primary outcome in the interventional group.

Seo et al reported a satisfactory brain relaxation (primary outcome) in 65% of patients who received the same dose of 20% mannitol as in the conventional group.^[8]^ We hypothesized that the primary outcome will be at least 55% in the interventional group to consider that hypertonic lactate sodium infusion provides a clinically relevant brain relaxation for supratentorial brain tumor resection.

A sample size of 25 patients was calculated to achieve a measurement accuracy of the primary outcome of 20% in the interventional group. In this phase II pilot study, 2 groups of patients are included to check whether the expected rate of the primary outcome is the same in the conventional group as in the study from Seo et al^[8]^ and to provide reliable data for further studies. Thus, the inclusion of a total sample size of 50 patients (25 patients per group) is planned.

### 3.12. Statistical analysis

The primary outcome will be described in the interventional group using mean and the 95% confidence interval of the mean. The normality of the distribution of continuous variable will be tested using the Shapiro–Wilk test. The interventional and conventional groups will be compared based on an intention-to-treat analysis. Intergroup comparisons will be conducted using the Mann–Whitney *U* or Student *t* tests for quantitative variables, depending on the distribution of data, and using Fisher’s exact test or the Chi-square test for qualitative variables. The significance level is fixed at 0.05. No interim analysis is planned.

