### 3.8. Outcome measures

The primary outcome is the proportion of satisfactory brain relaxation, defined as brain relaxation score of 3 or 4. Brain relaxation is assessed immediately after opening the dura by the neurosurgeon in charge of the patient blinded to the treatment allocated. The assessment of brain relaxation is performed using a validated 4-point scale,^[21]^ with: 1 = bulging brain; 2 = firm brain; 3 = satisfactorily relaxed; and 4 = perfectly relaxed).

Secondary outcomes are proportion of patients requiring a rescue therapy to improve the degree of brain relaxation during surgery; blood pH, serum osmolality, natremia, kaliemia, and lactatemia at baseline (before skin incision), and at 30 minutes, 60 minutes, 180 minutes, 24 hours, and 48 hours after the end of osmotherapy (either mannitol or hypertonic sodium lactate); serum levels of S100B and NSE proteins at baseline and at 24 hours and 48 hours after the end of osmotherapy; postoperative recovery assessed by the Glasgow Coma Scale on day 1 and on day 2 after surgery and by the Karnofsky performance status on day 30 after surgery; cognitive performance at baseline (the day before surgery) and on day 2 after surgery; volume of postoperative brain edema assessed on brain MRI performed on day 2 after surgery; and postoperative morbidity and mortality on day 30 after surgery.

Cognitive performance is assessed the day before surgery and on day 2 after surgery using a battery of validated neuropsychological tests during a 20-min face-to-face interview with an investigator who was specifically trained by a neuropsychologist (GC) prior the start of the study. Seven neuropsychological tests are performed to explore 5 different cognitive domains: (a) attention, using the Trail Making Test, part A; (b) executive function, using the Trail Making Test, part B and the semantic-phonemic switching verbal fluency test; (c) verbal fluency, using the Isaacs Set Test and the semantic-phonemic clustering verbal fluency test; (d) learning and episodic verbal memory, using the Memory Impairment Screen test; and (e) verbal short term and working memory, using the forward and reverse digit span memory test.

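### The binary primary outcome is to be summarised by a mean with the confidence interval of a mean; section 3.12 should name a proportion with a binomial interval

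*Protocol article*

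**What the plan says.** Section 3.8 of the protocol article, in line with the abstract, makes the outcome binary for each patient: "The primary outcome is the proportion of satisfactory brain relaxation, defined as brain relaxation score of 3 or 4".

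Section 3.11 uses that rate to size the trial: "A sample size of 25 patients was calculated to achieve a measurement accuracy of the primary outcome of 20% in the interventional group". It sets a relevance level, "We hypothesized that the primary outcome will be at least 55% in the interventional group", and cites satisfactory relaxation "in 65% of patients who received the same dose of 20% mannitol as in the conventional group" as the reference.

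Section 3.12 describes the result differently: "The primary outcome will be described in the interventional group using mean and the 95% confidence interval of the mean". It does name methods for categorical data, "using Fisher’s exact test or the Chi-square test for qualitative variables", but only for comparisons between groups. It names no interval for a single proportion.

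**The concern.** Three sections treat the primary outcome as a proportion, and the analysis section treats it as a mean. This is a stated choice that does not match the outcome, rather than a detail left open.

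Two things are at stake. First, the outcome is derived from a 1-4 score, so an analyst could take the mean to be the mean score, which is not what was defined or sized. Second, if the mean of 0/1 values is meant, the usual interval of a mean relies on a normal approximation that breaks down at high success rates with 25 patients.

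The Key Points say that the trial is not powered to compare the groups, and its size rests on precision in one arm. This interval is therefore the main inferential result.

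**Working it through.** **Inputs.** n = 25 in the interventional group; accuracy 20%; rates 55% and 65% (all section 3.11); 95% interval (section 3.12). Assumptions, because the article does not say: the accuracy is the absolute half-width of a two-sided 95% interval, and all 25 patients are evaluable.

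**Step 1. Reproduce the plan's figure.** For a single proportion, n = 1.96² × p(1 − p) / 0.20².
- p = 0.50: 24.01, so 25
- p = 0.55: 23.77, so 24
- p = 0.65: 21.85, so 22

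The stated 25 follows from p = 0.50. The sizing was done on a proportion.

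**Step 2. Half-widths at n = 25.** Write p̂ = k/25.
- Normal: 1.96 × √(p̂(1 − p̂)/25)
- t interval of the mean of 0/1 data: 2.064 × √(p̂(1 − p̂)/24)

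| Responders | Normal | t | Wilson | Clopper-Pearson |
|---|---|---|---|---|
| 12 or 13 of 25 (widest) | 19.6 | 21.0 | 18.2 | 20.45 |
| 14 of 25 | 19.5 | 20.9 | 18.1 | 20.3 |
| 16 of 25 | 18.8 | 20.2 | 17.6 | 19.75 |

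At 14 of 25 (56%) the intervals are: normal 36.5% to 75.5%, t 35.1% to 76.9%, Wilson 37.1% to 73.3%, Clopper-Pearson 34.9% to 75.6%.

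**Step 3. Exact coverage.** For a true rate p, sum the Binomial(25, p) probabilities of every count k whose interval contains p.

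| True rate | Normal | t | Wilson | Clopper-Pearson |
|---|---|---|---|---|
| 55% | 93.03% | 95.69% | 95.69% | 97.40% |
| 65% | 94.25% | 94.25% | 94.25% | 98.10% |
| 75% | 89.31% | 95.72% | 93.82% | 98.22% |
| 80% | 88.44% | 89.62% | 92.58% | 97.89% |
| 85% | 89.90% | 89.90% | 95.73% | 97.48% |
| 90% | 91.87% | 92.59% | 96.66% | 99.05% |
| 95% | 72.14% | 72.14% | 96.59% | 99.28% |

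At 80%, the normal interval covers only for 16 to 22 responders: at 15 its upper limit is 79.2%, and at 23 its lower limit is 81.4%. At 95%, almost all of the loss comes from 25 of 25. That result has probability 0.95²⁵ = 27.7%, and its interval is the single point 100%.

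**Step 4. Impossible limits.**
- At 22 of 25 the upper limit is 100.7% (normal) or 101.7% (t). It also exceeds 100% at 23 and 24.
- At 25 of 25 both intervals have zero width. Wilson gives 86.7% to 100% and Clopper-Pearson 86.3% to 100%.
- The chance of 22 to 24 responders is 0.05% at a true rate of 55%, 1.0% at 65%, 23% at 80% and 45% at 85%.

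**Step 5. The other reading.** Suppose the mean score in 25 patients is 2.6 (total 65). Eight patients at 4, sixteen at 2 and one at 1 give 32 + 32 + 1 = 65, with 8/25 = 32% satisfactory. Twenty at 3 and five at 1 give 60 + 5 = 65, with 20/25 = 80%. One mean score can thus lie on either side of the 55% level.

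**The case against.** The strongest reply is that this is loose wording. The mean of 0/1 values is the proportion, so the point estimate is unaffected. At the plan's own rates the interval works: at 55% and 65% the t interval covers exactly as well as Wilson. Between-group tests for categorical data are appropriate, the trial is a descriptive pilot, and the precise interval formula is often left to an analysis plan that is not shown. All of this stands, and it limits the point to one sentence with no effect on sample size or conduct.

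It does not remove the point. The article is not silent; it names a summary that does not match its outcome. The hypothesis in section 3.11 is a floor, so high rates remain possible.

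A reader might infer more than the documents support:
- **That the plan misses its 20% accuracy.** Only a t interval does so, by about 1 point at most (21.0 against 20), and the article never names t. The normal interval stays within 19.6 points at every possible result. Clopper-Pearson, a valid choice, also exceeds 20 slightly, so a small excess is no sign of an invalid analysis.
- **That the limits are invalid at 25 patients in general.** Near 55% to 65% they lie inside 0 to 100% with adequate coverage.
- **That the wrong variable will be analysed.** Sections 3.8 and 3.11 consistently speak of a rate, so the mean-score reading is possible but the less likely one.

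**Conclusion.** The point holds as a mismatch between the defined outcome and its stated summary. The interval of a mean is adequate around 55% to 65% (coverage 93.0% to 95.7%) and unreliable at about 80% or more. There, coverage is 88.4% (normal) or 89.6% (t) at 80% and 72.1% for both at 95%. It does not fall steadily in between; at 90% it is about 92% to 93%. The normal interval is already at 89.3% at a true 75%. Limits above 100% at 22 to 24 of 25, and zero width at 25 of 25, follow directly from the formulas.

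The practical weight depends on the true success rate, which the article says is unknown. The figures assume 25 evaluable patients and a two-sided 95% interval. The sample size of 25 stands. The wording should be settled before the data are analysed, because it governs the primary result.

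**What to change.** Replace the sentence in section 3.12 with, for example: *The primary outcome will be reported as the number and proportion of interventional-group patients with a score of 3 or 4, with a two-sided 95% confidence interval for a binomial proportion by the [Wilson or Clopper-Pearson] method. The 1-4 scores will be shown as counts per category.*

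Either method is acceptable if it is fixed in advance; name the same one in section 3.11. With Wilson the stated accuracy can stay, since the half-width is at most 18.2 points. With Clopper-Pearson, restate the accuracy as about 20.5 points at worst (20.45 at 12 or 13 of 25; 20.3 at 14 of 25).

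The cost is one sentence, plus a few words in section 3.11. Recruitment, conduct and sample size do not change.

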### 3.5. Study outline

Eligible patients are screened and informed during the anesthesia consultation. Written informed consent is obtained the day before surgery by investigators after oral explanation of the study. After written informed consent is obtained, patients are randomized using a computer-generated randomization list implemented on the CleanWeb web-based system (Telemedicine Technologies, France).

After randomization, a first cognitive assessment using a battery of validated neuropsychological tests (see below) is performed by an investigator who was specifically trained by a neuropsychologist (GC) prior to the start of the study. Patient characteristics, past medical history including ASA physical status, type of brain tumor, preoperative management of brain tumor (corticosteroid therapy, antiepileptic therapy, chemotherapy, and/or radiotherapy), preoperative Karnosky performance status, and preoperative neurological status including Glasgow Coma Scale are collected. Midline shift, brain tumor size, and localization, and the size of peritumoral edema are extracted from the preoperative brain imaging [either brain magnetic resonance imaging (MRI) or computed tomography scan]. Included patients undergo a first cognitive assessment using a battery of validated neuropsychological tests (see below).

On arrival in the operating room, standard monitoring (General Electric Healthcare) is put in place. A peripheral venous catheter dedicated to anesthetic drug infusion is inserted in a forearm vein. All patients receive intravenous anesthesia based on manually driven target-controlled infusion of propofol and remifentanil aiming to maintain bispectral index (BIS) values between 40 and 60. All patients are paralyzed using nondepolarizing neuromuscular blocking agent (either cisatracurium or atracurium).

After induction of anesthesia, patients are intubated, and tidal volume and respiratory rate are set to maintain the end-tidal carbon dioxide between 35 and 40 mm Hg. Inspired oxygen fraction is adjusted to obtain a pulse oximetry ≥ 95%. A second peripheral venous catheter, a urinary catheter, and an indwelling arterial catheter introduced in a radial artery are implemented.

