### 3.6. Randomization, allocation concealment, and blinding

Randomization is performed the day before surgery using the CleanWeb web-based system (Telemedicine Technologies, France). A computer-generated permuted-block randomization list with varying block sizes (ratio 1:1) was implemented on the website at the beginning of the study by an independent data manager. The block size is unknown to the investigators. When written informed consent was obtained, the investigator entered data online regarding each patient to enable inclusion and randomization. The treatment randomly allocated to the patient is immediately provided to the investigator by the website.

Patients and outcome assessors (neurosurgeons) are blinded to the treatment allocated.

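### Secondary outcomes with a pre-treatment value are compared by unadjusted tests chosen by a normality pre-test, which gives up precision available from data already collected

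*Protocol article*

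**What the plan says.** Section 3.12 of the protocol article gives one rule for every quantitative variable. First, "The normality of the distribution of continuous variable will be tested using the Shapiro–Wilk test". The arms are then compared with Mann–Whitney U or Student t "tests for quantitative variables, depending on the distribution of data". The comparison is a planned one: "The interventional and conventional groups will be compared based on an intention-to-treat analysis", and "The significance level is fixed at 0.05". No covariate, change score, ANCOVA or repeated-measures model is named.

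Section 3.8 lists secondary outcomes measured before and after treatment:

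- pH, osmolality, sodium, potassium and lactate, at baseline and at five later times;
- S100B and NSE, at baseline, 24 hours and 48 hours;
- "cognitive performance at baseline (the day before surgery) and on day 2 after surgery; volume of postoperative brain edema", the cognitive part being a battery of seven tests.

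Karnofsky status on day 30 is also an outcome, and section 3.5 collects it preoperatively. The same section says: "Midline shift, brain tumor size, and localization, and the size of peritumoral edema are extracted from the preoperative brain imaging".

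On size, section 3.11 states that "the inclusion of a total sample size of 50 patients (25 patients per group) is planned". Section 3.6 describes 1:1 permuted blocks and names no stratification factor.

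**The concern.** A patient's value before surgery usually predicts part of the value afterwards. A two-sample test on the follow-up value leaves that predictable part in the error term. With 25 patients per arm and no stratification factor named, neither size nor design makes up for it.

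The article says that the trial should give reliable data for further studies (section 3.11). Secondary estimates with wider intervals than necessary serve that aim less well.

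The pre-test adds a separate problem. It chooses between a comparison of means and a comparison of ranks after the data are seen. For an analyte followed over several times, the reported quantity could change from one time to the next.

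**Working it through.** **Inputs from the article.** 25 per arm, 1:1 allocation (sections 3.6 and 3.11); significance level 0.05 (section 3.12), taken as two-sided because sidedness is not stated.

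**Assumed input.** The correlation r between baseline and follow-up is not given. It is shown at 0.3, 0.5 and 0.7.

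**Step 1: the plan's own figure.** Reading the 20% accuracy in section 3.11 as the half-width of a 95% confidence interval, n = 1.96² × p(1 − p) / 0.20². This gives 24.0, rounded up to 25, at p = 0.50, and 23.8, rounded up to 24, at p = 0.55. The stated 25 is reproduced. It concerns the primary proportion only and does not depend on this point.

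**Step 2: gain from adjustment.** ANCOVA multiplies the variance of the treatment difference by 1 − r². Interval width scales with √(1 − r²), and the equivalent unadjusted arm size is 25 / (1 − r²). The difference detectable with 80% power is (1.96 + 0.84) × √(2/25) × √(1 − r²), in SD units.

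| r | Variance cut | Interval narrower by | Equivalent n per arm | Detectable difference |
|---|---|---|---|---|
| unadjusted | – | – | 25 | 0.79 SD |
| 0.3 | 9% | 5% | 27 | 0.76 SD |
| 0.5 | 25% | 13% | 33 | 0.69 SD |
| 0.7 | 49% | 29% | 49 | 0.57 SD |

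**Step 3: cost of adjustment.** Estimating one extra slope inflates the variance by about 1/(N − 4) = 1/46, or about 2%, with N = 50. The table leaves this out. Adjustment breaks even where r² is about 0.02, that is, r of about 0.15.

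**Step 4: simulation of the stated rule.** There were 3,000 runs per scenario, with a true difference of 0.6 SD and Shapiro–Wilk applied to each arm (the article does not say how it is applied).

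- Normal data: power was 0.54 to 0.56 under the pre-test rule, against 0.57, 0.67 and 0.83 with ANCOVA at r = 0.3, 0.5 and 0.7.
- Lognormal data: 0.51 to 0.53, against 0.58, 0.66 and 0.82 with ANCOVA on the log scale.
- No true difference: the pre-test rule rejected in 0.043 to 0.058 of runs, so type I error was not visibly inflated.
- Choice of test: about 10% of comparisons on truly normal data went to Mann–Whitney. Two checks at 5% each predict this: 1 − 0.95² = 9.75%.

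**Step 5: chance imbalance.** A standardised baseline difference has SD √(2/25) = 0.283, so the chance that it exceeds 0.5 SD in either direction is 7.7% for any one variable. Given a 0.5 SD imbalance, the unadjusted follow-up difference is shifted on average by r × 0.5, which is 0.15, 0.25 or 0.35 SD at the three values of r.

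**Step 6: change scores.** The article does not say whether raw values or changes are tested. Change scores have variance 2(1 − r) relative to the raw value: 1.4, 1.0 and 0.6, against 0.91, 0.75 and 0.51 for ANCOVA. Testing changes would therefore not remove the point.

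**The case against.** **This is detail for the analysis plan.** The article is condensed, and covariate adjustment of secondary outcomes often sits in the SAP, which is not shown. That would answer a complaint about an omission. Here the article names the tests for all quantitative variables, so the point is about a stated choice. A fuller SAP may already improve on it.

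**The tests are valid.** This stands. Unadjusted comparison of randomised arms is unbiased, and the unadjusted standard error already allows for chance imbalance, so the 7.7% is not a further error on top of it. A reader might infer that the pre-test inflates type I error; the simulation does not show that.

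**The trial is descriptive and disclaims comparative power.** Also true. The primary outcome is binary, has no baseline value, and is described in the interventional arm. This limits the weight, but a small trial meant to inform later ones still benefits from tighter estimates.

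**Several stronger readings go beyond the text.**

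- That postoperative differences will be dominated by preoperative ones: baseline explains r² of the variance, which is at most 49% over the range shown, and no r is given.
- That five analytes at five later times mean 25 separate tests: section 3.12 does not say that each time is tested alone.
- That the arms will be tested against each other at baseline: section 3.8 lists baseline as a measurement time, and no such test is scheduled.
- That preoperative edema is a baseline for the edema outcome: the first is a size from MRI or CT, the second a volume on MRI after resection.

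**Some baselines are not ready for use.** This stands for two of them. Section 3.5 defines the baseline sample as taken just before incision, while section 3.9 puts the S100B and NSE baseline on the day before surgery. The first cognitive assessment follows randomisation, the allocation is shown to the investigator at once, and only patients and neurosurgeons are stated to be blinded.

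**Conclusion.** The point holds as one of efficiency and of a common scale, for secondary outcomes only. The rule in section 3.12 leaves unused the pre-treatment values of the cognitive tests, the five chemistry variables, S100B, NSE and Karnofsky status. It does not make any comparison invalid, and it does not touch the primary analysis or the sample size.

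The size rests wholly on the assumed r. At 0.3 the gain is close to nothing in power; at 0.7 it is worth nearly doubling the arms. Early post-infusion chemistry may lie at the low end. Day-2 cognition and the injury markers are likelier to benefit.

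The concern about the pre-test depends on reading the rule as applied to each time point, which the article neither states nor excludes. The harm would be a comparison whose meaning is chosen by the data, not false positives. The change is worth making because it is cheap.

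**What to change.** For outcomes with a pre-treatment value, replace the Shapiro–Wilk step and the two-sample tests by analyses fixed before unblinding:

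- **Cognitive tests:** ANCOVA of the day-2 value on arm and baseline, for each test.
- **pH, sodium, potassium, lactate, osmolality, S100B and NSE:** one repeated-measures model per analyte with baseline, arm, time and arm-by-time, and with the scale for skewed markers (for example, logarithmic) chosen in advance.
- **Karnofsky status:** adjustment for the preoperative value, if preferred by a method suited to an ordinal score.
- **Postoperative edema volume:** preoperative edema size may enter as a prognostic covariate, described as such.
- **Reporting:** adjusted differences with 95% confidence intervals.

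First reconcile sections 3.5 and 3.9 on when the S100B and NSE baseline is drawn, and confirm whether the cognitive assessor is unaware of allocation.

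The cost is revised analysis wording and a little more analysis work, with no new data or patient procedures. If r is near zero, about 2% in variance is lost.
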